**Protocols and Procedures**

Participants will reside as inpatients in the Clinical Research Center for the duration of this study. Participants will be required to refrain from illicit and prescription drug use for the duration of the study and this will be confirmed with daily urine and breath alcohol level testing. Caffeine and food will be prohibited during and 1-2 hours before study sessions.

Experimental sessions will be conducted at approximately the same time of day for a given participant. Experimental sessions will be several hours in duration and will be conducted in a quiet room on the GCRC with research and medical staff present. The room will contain an experimental station, equipped with a response console attached to a personal computer and video monitor. Participants will register selections by pressing a key on the response console. Heart rate, EKG, and blood pressure will be recorded throughout experimental sessions using a Scout automatic monitoring system. Medical personnel will monitor cardiac function during drug administration periods and for 2 hours following drug administration.

Participants will be admitted to the hospital and will be randomized to study drug or placebo on the following day. During the next several days staff will familiarize participants with upcoming procedures and participants will complete a mock version study procedures. Participants will remain seated during experimental sessions except for brief visits to the lavatory. The first 30-min of all sessions will be devoted to the collection of baseline data and participant preparation.

**Experiments**

We propose assess effects of disulfiram and placebo on cocaine self-administration using an established laboratory model. Each participant will complete the experiment during treatment with placebo and disulfiram. The order in which a participant will receive disulfiram or placebo will be randomized to control for order effects.

At 1pm on days 5 and 7, participants will choose between a dose of cocaine (0mg or 20mg) or a monetary alternative in each of 10 subsequent choices. The same dose of cocaine, 0mg or 20mg, will be available for all 10 choices on a given day and each dose will be assigned to either day 5 or 7 in a randomized, double-blind manner. The monetary alternative will be $.05, $.05, $.05, $.05,$1, $4, $7, $10, $13, or $16 cash, presented in that order. Selections will be made at 15-minute intervals, and participants will receive cocaine doses or cash immediately after indicating their choice, providing vital signs remain within preset intervals. Heart rate variability measures will be conducted throughout the choice session as well.

Study drug will be discontinued on day 7, after completion of the experimental sessions. On days 1, 4 and 8, neurocognitive assessments and continous heart rate recording will be completed starting at 3:00 PM. Subjects will be asked to refrain from smoking tobacco for at least 2 hours before the assessment.

Subjects will be monitored through day 8 and on day 9 they can either go home and return to complete the procedures under the alternate condition (placebo vs. disulfiram), or they can stay in the hospital and start the alternate study drug on the next day.

Day 1 Admit to the CRC, complete neurocognitive testing with continuous heart rate recording.

Day 2 *Randomize to study drug 1. The order in*

which participants *receive disulfiram*

*and placebo will be randomized*

Day 3

Day 4 Neurocognitive testing with continuous heart rate recording.

Day 5 Choice session 1

*Participants will choose between cocaine (0mg or 20mg) and money*

Day 6

Day 7 Choice session 2

*Participants will choose between cocaine (0mg or 20mg, reverse of day 5) and money*

Day 8 Monitor. Neurocognitive assessment with continuous heart rate recording.

Day 9 Discharge or subjects can remain in hospital for study part 2

The total possible dose that a patient can receive during choice sessions is 200mg, and the total dose they can receive over the study visit is 200mg.

A participant’s day will begin at 7 am with study drug dosing followed by breakfast. Lunch will be served at 11:30. At 1 pm participants will enter the choice component of the experiment. This will be completed by 5 pm, after which dinner will follow at 6 pm. The dependent measures will be (1) the maximal completed ratio attained for cocaine within a session, (2) baseline (prior to the first sample dose) subjective effects (assessed using visual-analogue scales) and cardiovascular indices, (3) effects of the sample dose of cocaine on subjective effects, cardiovascular, and performance measures, and (4) effects of repeated cocaine doses on subjective effects and cardiovascular measures using time as a within-group factor (relevant to sessions in which cocaine is selected). The planned comparisons for each measure are disulfiram versus placebo at each dose of cocaine (Haney et al 1998).

*Follow-up of Study Participant*s

Participants will return to the study site at 2 weeks and at 4 weeks following completion of each study. Adverse event, drug use, and clinical information will be completed, and participants will receive compensation for participating in the study.

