**LABORATORY MODELS OF COCAINE SELF ADMINISTRATION**

**Study Design Overview**

We propose to investigate effects of disulfiram 250mg compared to placebo on cocaine self-administration using a human laboratory model established by a group at Johns Hopkins ([name]). This investigator has agreed to serve as a consultant for this project, ensuring that the procedures followed are appropriate and that interpretation of the data is consistent with prior studies. Letters from the consultants are included in the appendix

Participants will be admitted to the hospital for 2 study visits. The visits follow the same layout, and participants will receive study drug during one visit and placebo during the other. Participants will be admitted to the hospital and will be randomized to study drug or placebo on the following day. During the next several days staff will familiarize participants with upcoming procedures and participants will complete a mock version study procedures. Participants will remain seated during experimental sessions except for brief visits to the lavatory. The first 30-min of all sessions will be devoted to the collection of baseline data and participant preparation.

At 1pm on days 5 and 7, participants will choose between a dose of cocaine (0mg or 20mg) or a monetary alternative in each of 10 subsequent choices. The same dose of cocaine, 0mg or 20mg, will be available for all 10 choices on a given day and each dose will be assigned to either day 5 or 7 in a randomized, double-blind manner. The monetary alternative will be $.05, $.05, $.05, $.05,$1, $4, $7, $10, $13, or $16 cash, presented in that order. Selections will be made at 15-minute intervals, and participants will receive cocaine doses or cash immediately after indicating their choice, providing vital signs remain within preset intervals. Heart rate variability measures will be conducted throughout the choice session as well.

Study drug will be discontinued on day 7, after completion of the experimental sessions. On day 8, the neurocognitive assessment and continuous heart rate recording will be repeated (as on days 1 and 4), starting at 3:00 PM. Again, subjects will be asked to refrain from smoking tobacco for at least 2 hours before the assessment.

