Subjects will be monitored through day 8 and on day 9 they can either go home and return to complete the procedures under the alternate condition (placebo vs. disulfiram), or they can stay in the hospital and start the alternate study drug on the next day.

Subjects can be re-admitted to the study after several days or weeks and the experiment will be repeated during treatment with the alternate study drug (placebo or disulfiram). The total possible dose of cocaine that a patient can receive during choice sessions is 200mg, and the total dose they can receive over the study visit is 200mg.

In both studies, the participants will respond by pressing a response button or lever, depending on whether the patient controlled analgesia (PCA) pump or the Med Associates device incorporating FDA-approved Baxter infusion pump is utilized. When money choices have been selected, cocaine choices are unavailable for the remainder to the time-out period. For the purpose of these studies, the devices are interchangeable.

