**Statistical Analysis**

*Power analysis.* The proposed sample size of 60 should allow detection of small-to-medium effects (approximately f=.17) when comparing conditions (within-subject factors) using repeated measures analyses with power=.80 and two-tailed alpha=.05. This effect size translates to a difference of approximately 1/3 standard deviation units (d=.33) in differences in means across conditions (Cohen 1988; Elashoff 2000). A moderate within-subject correlation of .5 was assumed across conditions. We have conservatively powered the study for 2-tailed tests to cover the range of primary and secondary hypotheses; however, since we expect disulfiram to reduce cocaine choices, power would be greater for a one-tailed test of the primary hypothesis in each experiment. This sample size will also allow for detecting medium-to-large effects in assessing secondary hypotheses (such as a linear trend in cocaine dose-response) with Bonferroni correction for post hoc comparisons. The above power analysis has been calculated assuming no order effects for disulfiram vs. placebo conditions; however, if order effects are detected, then analyses will assess effects within order conditions, with a corresponding decrease in power allowing detection of medium effect sizes (f=.26) across condition.

*Statistical Analysis.* Descriptive statistics will be used to summarize sample characteristics on all measures, as appropriate to measurement characteristics of individual variables. Order effects (for disulfiram vs placebo) will be assessed using repeated measures ANOVA to determine equivalence; because of random assignment, no differences are anticipated. However, if significant differences are found, then primary analyses will examine effects within each order condition.

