Repeated measures ANOVA will be used to assess effects of disulfiram within each experiment. For each experiment, a general linear model will include within-subject factors representing condition (disulfiram vs. placebo) and cocaine dosage. Separate analyses will be conducted for each outcome measure. If outcome measures are substantially non-normal, then a GEE (generalized estimating equations) approach will be used for testing hypotheses instead of the general linear model for repeated measures (Burton et al 1998). This extended approach allows analysis of non-normally distributed data (e.g. binomial or gamma) as well as inclusion of a correlated covariance structure to accommodate within-subject effects.

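### Cocaine dose is randomised to day 5 or day 7 with no link between visits and no session-day term in the model, a small avoidable loss of precision in the dose-specific comparisons

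*Protocol*

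**What the plan says.** Each visit has one choice session on day 5 and one on day 7. One session offers 0 mg and the other 20 mg, and "each dose will be assigned to either day 5 or 7 in a randomized, double-blind manner" (Protocol, Experiments; the same rule is in Study Design Overview). The only stated constraint works within a visit: the day-7 entry in the schedule reads "Participants will choose between cocaine (0mg or 20mg, reverse of day 5) and money".

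Two statements in Study Design Overview come closest to a link between visits: "The visits follow the same layout" and "the experiment will be repeated during treatment with the alternate study drug". Neither mentions which cocaine dose falls on which day.

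On analysis, Experiments states: "The planned comparisons for each measure are disulfiram versus placebo at each dose of cocaine". Statistical Analysis specifies that "a general linear model will include within-subject factors representing condition (disulfiram vs. placebo) and cocaine dosage", and the only order check is for drug order: "Order effects (for disulfiram vs placebo) will be assessed using repeated measures ANOVA to determine equivalence". Session day appears in neither. The time factor mentioned in Experiments refers to repeated doses within a session.

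**The concern.** The comparison at 20 mg sets one session from the disulfiram visit against one from the placebo visit. If 20 mg fell on day 5 in one visit and day 7 in the other, the participant's difference contains a day-7 versus day-5 shift as well as the drug effect.

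The two days are not interchangeable by design. Study drug is taken each morning. If the first capsule is on day 2, the day of randomisation, a day-5 session follows 4 capsules (days 2 to 5) and a day-7 session follows 6 (days 2 to 7). Day 7 also comes after an earlier choice session with the opposite dose.

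What is at stake is precision. The shift adds variance to the dose-specific comparisons, although it comes from a factor that the trial itself randomises and could account for at almost no cost.

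**Working it through.** **Inputs.** From Statistical Analysis: N=60, d=.33 (f=.17), within-subject correlation .5, two-sided alpha .05, stated power .80. The day shift delta is not in the documents, so a range is assumed. Independent 1:1 assignment of dose to day at each visit is also assumed.

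**The plan's own figure.** With correlation .5, the SD of the paired difference is √(2(1−.5)) = 1. The exact paired t-test at N=60 gives power .71 for d=.33 and .74 for d=.34 (f=.17), not .80. That mismatch is a separate matter; .71 is the baseline here.

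**Discordance.** P(20 mg on different days in the two visits) = 2 × .5 × .5 = .50. That is 30 of 60 expected, with a 95% range of 22 to 38. The same holds at 0 mg.

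**Dose-specific comparison.** Let a and b be 1 if 20 mg is on day 7 under disulfiram and placebo respectively, and 0 otherwise. The difference at 20 mg gains delta(a−b), which is −delta, 0, 0 or +delta with probability 1/4 each. Its mean is 0 and its variance delta²/2, so the variance of the difference becomes 1 + delta²/2. Power is computed at .33/√(1 + delta²/2).

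| delta | variance | power, no day term (d=.33) | power, no day term (d=.367) |
|---|---|---|---|
| 0 | 1.000 | .71 | .80 |
| 0.2 | 1.020 | .70 | .79 |
| 0.33 | 1.054 | .69 | .78 |
| 0.5 | 1.125 | .66 | .75 |
| 1.0 | 1.500 | .54 | .63 |

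The last column uses the difference that 60 completers can detect with about 80% power. In simulation (40,000 runs each at delta 0, 0.33, 0.5 and 1.0), a day term holds power at about .70 for d=.33 and .79 for d=.367.

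**Bias and type I error.** With a true difference of .33, the mean unadjusted estimates at delta 0.33, 0.5 and 1.0 were .331, .331 and .329. With a true difference of 0, rejection rates were .050, .051 and .050.

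**Condition main effect.** The 0 mg session takes the other day, so its difference gains delta((1−a)−(1−b)) = −delta(a−b). Averaged over the two doses, the day terms sum to zero.

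**Condition-by-dose interaction.** Here the two terms reinforce each other: 2·delta(a−b), with variance 4 × delta²/2 = 2·delta². With all correlations .5, the contrast without a day effect has variance 4 × (1−.5) = 2. The ratio is 1 + delta², or 1.25 at delta 0.5 and 2.0 at delta 1.0.

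**Effect of longer exposure under disulfiram only.** The difference gains delta·a, with variance delta²/4 (total variance 1.0625 at delta 0.5 and 1.25 at 1.0). A plain day term removes only part of it. The regression of a on (a−b) leaves 1/4 − (1/4)²/(1/2) = 1/8, that is delta²/8. The rest needs a day-by-condition term.

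**The case against.** The strongest reply is that the design is sound and the loss probably small. Randomising the dose day prevents systematic confounding of dose with day, and leaving the visits unlinked protects the blind, since a repeated order would make visit 2 predictable. Statistical Analysis states power for comparing conditions, and in the condition main effect an additive day shift cancels. All of this stands, and it confines the point to the comparisons at each cocaine dose and the interaction.

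The mechanisms are also open to question. Nothing says that participants are told day 7 reverses day 5. The first four money alternatives are $.05, so the dose can be sampled on day 5 at almost no cost. For the 20 mg comparison, any earlier session in the same visit is always 0 mg, so carry-over from an active session within the visit can affect only the 0 mg comparison. The exposure mechanism operates only under disulfiram, does not depend on discordance between visits, and follows delta²/4. These arguments make a large delta less likely but do not show that it is zero.

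Finally, a statistical analysis plan could add a day term, and blocking is often left to the list. But the protocol does name its model factors and the order effect to be checked, and both omit a factor that it randomises. An analysis plan cannot create balance after randomisation.

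A reader might infer that the drug comparison is biased. It is not: the shift has mean zero under randomisation. Chance day imbalance can move one trial's estimate by about 1.96 × √(.5/60) × delta = 0.18 × delta, but that is the same noise already counted in delta²/2, not a second harm.

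**Conclusion.** The point holds as a minor precision improvement. The documents give no link or balance of dose-day order between visits and no session-day term, while planning comparisons at each cocaine dose. The cost to those comparisons at d=.33 is 1 to 2 power points if the day shift is 0.2 to 0.33 SD, 5 points at 0.5 and 17 at 1.0. A shift of 1.0 would be three times the drug effect that the trial is sized for, so the upper end should not be read as the expected loss.

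The figures rest on an assumed delta and an additive shift that is equal at both cocaine doses. The half discordant also depends on independent 1:1 assignment at each visit. The protocol states neither independence nor the ratio, so the half is the natural reading and not a stated fact. The documents do not support reading this as a loss of power for the overall disulfiram effect.

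**What to change.** 1. Add session day (5 versus 7) as a within-subject term to the model in Statistical Analysis. Because day varies within participant independently of the condition-by-dose layout, fit it as a mixed model or with the GEE approach that the protocol already names as its alternative.
2. Add a day-by-condition term as a sensitivity analysis, to cover an effect of longer exposure under disulfiram only.
3. Build the randomisation list jointly over drug order and dose-day order, so that at each cocaine dose day 5 and day 7 occur equally often under disulfiram and placebo. Balance keeps an additive day shift out of the estimate, and the day term keeps it out of the standard error, so both are needed.

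Fixing the same day order at both visits is not recommended, because it makes visit 2 predictable.

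The cost is one or two degrees of freedom and a revised list, with no added sessions or participants. If there is no day effect, the day term costs about 1 power point (.71 to .70 in simulation).

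### The first listed outcome is a completed ratio and two others rest on a sample dose; the experiment has neither, and cocaine choices, the subject of the primary hypothesis, are not listed

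*Protocol*

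**What the plan says.** The Experiments section describes the task: "participants will choose between a dose of cocaine (0mg or 20mg) or a monetary alternative in each of 10 subsequent choices". Within a session the cocaine dose is fixed and the cash alternative rises from $.05 to $16. The paragraph on self-administration procedures, under Assessments, says that one push of a button on the pump delivers the dose at once.

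The same Experiments section later lists four dependent measures:

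1. "the maximal completed ratio attained for cocaine within a session"
2. "baseline (prior to the first sample dose) subjective effects", together with cardiovascular indices
3. "effects of the sample dose of cocaine on subjective effects, cardiovascular, and performance measures"
4. "effects of repeated cocaine doses on subjective effects and cardiovascular measures using time as a within-group factor", limited to sessions in which cocaine is selected

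It adds that, for each measure, disulfiram is to be compared with placebo at each cocaine dose.

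On the amount of cocaine, the section gives 200 mg as the most a participant can receive in the choice sessions and then says that "the total dose they can receive over the study visit is 200mg".

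The power analysis, under Statistical Analysis, names the quantity of interest: "since we expect disulfiram to reduce cocaine choices, power would be greater for a one-tailed test of the primary hypothesis". It also mentions "secondary hypotheses (such as a linear trend in cocaine dose-response" among the things the sample size would support.

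**The concern.** A completed ratio belongs to a schedule in which the number of responses needed for a dose is set and usually raised. In this task the cash offer rises and the response requirement does not. A sample dose is a dose given before the choices so that the participant knows what is on offer, and nothing in the day-by-day plan provides one. The list of outcomes therefore does not fit the experiment it is attached to, while the outcome that does fit, and that carries the primary hypothesis, is absent from it.

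The Statistical Analysis section runs a separate analysis for each outcome measure, so the list decides what is analysed. If it stays as it is, the first listed measure has no data. Someone must then decide what stands in for it, and how cocaine choice is to be summarised, possibly after results are known.

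**Working it through.** This is mainly a comparison of text, with two pieces of arithmetic.

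**Measure (1), the ratio.** The Study Design Overview and the Experiments section both describe ten choices at 15-minute intervals. The self-administration paragraph requires one button push per dose. The Overview mentions a lever as an alternative device and calls the devices interchangeable, but gives no number of presses. No passage sets a response requirement, so there is no ratio to complete and no maximum to record.

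**Measures (2) and (3), the sample dose.** The term occurs only in the list of measures. The day-by-day plan has choice sessions on days 5 and 7, one with 0 mg and one with 20 mg, and no other cocaine administration. The dose arithmetic agrees with that:

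- choice sessions in one visit: 10 × 20 mg + 10 × 0 mg = 200 mg
- stated maximum for the choice sessions: 200 mg
- stated maximum for the whole visit: 200 mg
- left for a sample dose: 200 − 200 = 0 mg

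Measure (3) also refers to performance measures. The only scheduled performance testing is the neurocognitive assessment on days 1, 4 and 8, none of which is a day on which cocaine is given.

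**Does the rest of the protocol fit the ten-choice task?** The payment section gives a maximum of $204.80 from choice sessions.

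- one session: 4 × $.05 + $1 + $4 + $7 + $10 + $13 + $16 = $51.20
- two sessions per visit, two visits: 4 × $51.20 = $204.80

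The payment figure is reproduced exactly. The dose and payment figures both match ten choices per session, so the list of measures is the part out of step.

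**The primary hypothesis.** The power analysis expects fewer cocaine choices under disulfiram and links this to the primary hypothesis. None of the four measures is a count, proportion or other summary of cocaine choices.

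**Measure (4).** Cardiovascular and subjective effects are assessed before and at 5 and 14 minutes after each cocaine dose, so this measure can be computed. It exists only where cocaine was chosen, and disulfiram is expected to change how often that happens.

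**The trend.** With two doses (0 and 20 mg) a linear trend has one degree of freedom and is the same test as the 0 versus 20 mg contrast.

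| Listed measure | Needs | Provided by the design? |
|---|---|---|
| (1) | a response-ratio schedule | no |
| (2) | a pre-session baseline | yes, but tied in wording to a sample dose |
| (3) | a sample dose | no |
| (4) | self-administered doses | yes, where cocaine is chosen |

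**The case against.** The strongest reply is that the intention is clear. The power analysis speaks of cocaine choices, the list does not label the ratio as primary, and an SAP may define a choice count. One could also read the ratio as the highest cash sum given up for cocaine. Part of this stands: the construct is recognisable, and first listed does not mean primary. But the text never defines the ratio that way, and the highest sum given up is a different summary from the number of choices. An SAP that defined a choice count would leave the protocol's own list in contradiction with its task.

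It might also be said that a sample dose could fall in the practice run of the procedures before the choice days. The protocol does not describe cocaine in that run, and the 200 mg statement leaves no room for it.

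A reader might infer more than the documents support:

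- **That measure (2) has no baseline.** The first 30 minutes of every session are set aside for baseline data, and effects are assessed before each dose. Only the reference to a sample dose is wrong.
- **That the linear trend cannot be tested.** It can; it is merely redundant.
- **That power is lost because the condition effect is averaged over both cocaine doses.** The protocol already plans disulfiram versus placebo at each dose, so the argument assumes a departure from the plan.
- **That measure (4) is invalid.** The protocol already limits it to sessions in which cocaine is selected. The payment section says that no participant chooses money every time, and the documents do not allow an estimate of how many sessions would have no cocaine dose.

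**Conclusion.** The point holds as an internal contradiction and should be corrected. Two of the four listed measures, (1) and (3), cannot be produced by the experiment as described. One, (2), needs rewording. One, (4), can be obtained but is conditional on choosing cocaine. The outcome of the primary hypothesis is missing from the list.

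This rests on the protocol's text and on 10 × 20 mg = 200 mg, with no outside assumption. It does not show that the trial lacks usable outcome data, because the choices are registered at the console in every session. What is left open is the exact summary of those choices, and that should be settled before data are seen.

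The sample size statement is unaffected by the renaming. Its effect size is purely standardised (d=.33), and the protocol gives no mean or standard deviation for any outcome, so no new calculation for the choice count can be made from it.

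**What to change.** Amend the list of dependent measures in the Experiments section, and align the Statistical Analysis section with it:

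- **Measure (1):** replace it with the number of cocaine choices out of the ten offered per session, and state this as the primary outcome. Keep the planned comparison of disulfiram with placebo at each cocaine dose, and say that the 20 mg session is the comparison that bears on the primary hypothesis.
- **Measure (2):** refer to the 30-minute pre-session baseline and drop the mention of a sample dose.
- **Measure (3):** reconcile it with the day-by-day schedule and the 200 mg statement, or delete it.
- **Measure (4):** label it as conditional on choosing cocaine, and preferably compare conditions at the same dose number, for example the first self-administered dose.
- **Minor:** remove the linear trend, or say that it is the 0 versus 20 mg contrast.

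The cost is a wording amendment. The choices, the baseline and the assessments after each dose are already collected.

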**Research Participants**

Each subject will complete procedures while receiving placebo and disulfiram. We anticipate that 75 volunteers will enter the study and that there will be a dropout rate of 20-30%, yielding a sample size of 60.

*Recruitment*

Potential participants will be recruited using flyers, print ads, and radio advertisements. Our experience from previous studies indicates that well-placed and maintained flyers coupled with print and radio spots are sufficient to maintain frequent calls to our toll-free number. Over a recent 12-month period, our recruitment center received approximately 2,600 calls from stimulant users interested in participating in our studies. From those contacts, approximately 10% of the callers were eligible to meet with our research staff for consultation. Roughly 20% of those callers attended an initial screening appointment and met general inclusion criteria for a non-treatment-seeking study involving cocaine or methamphetamine administration (fewer met stricter criteria for particular studies, as some studies require prior IV experience). Thus, our existing recruitment approach provided about 50 eligible participants per year. We can easily increase the intensity of recruitment efforts in to accommodate the recruitment needs of the proposed project.

Participants who call our toll-free number are informed about the *general* requirements of the study and appointments are scheduled for those who are interested. Participants are not informed about the specific inclusion/exclusion criteria in order to avoid participants tailoring their responses in order to enter the protocol. During a face-to-face interview with a study physician participants are given consent documents that are read to them if needed. Following completion of the informed consent process, participants are screened using the criteria below. At several times during the screening process, participants are informed that treatment is available and referrals are provided if desired. Following completion of the consent process, participants will an oral swab will be used to collect epithelial cells that will provide DNA for genotyping at the DBH locus. Subjects with all genotypes will be included in this study.

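### The planned by-dose comparisons are applied to the pre-cocaine baseline measure, splitting one question into two weaker tests; the condition main effect should be its planned comparison

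*Protocol*

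**What the plan says.** The Experiments section of the protocol lists four dependent measures. The second is "baseline (prior to the first sample dose) subjective effects (assessed using visual-analogue scales) and cardiovascular indices". The paragraph then fixes the contrast for all four: "The planned comparisons for each measure are disulfiram versus placebo at each dose of cocaine". No measure is exempted.

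The same section sets two choice sessions per visit, on days 5 and 7. One offers 0 mg and the other 20 mg, in randomized, double-blind order. Protocols and Procedures gives the first 30 minutes of every session to baseline data and preparation.

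The Statistical Analysis section says that "a general linear model will include within-subject factors representing condition (disulfiram vs. placebo) and cocaine dosage", with a separate analysis for each outcome measure.

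Other recordings are scheduled outside the choice sessions: "On days 1, 4 and 8, neurocognitive assessments and continous heart rate recording will be completed starting at 3:00 PM". They are not among the four dependent measures.

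**The concern.** A contrast by cocaine dose makes sense for a measure that the dose can affect. The baseline is collected before that session's dose is given or known, so the dose cannot have acted on it. Disulfiram versus placebo at 0 mg and disulfiram versus placebo at 20 mg are then the same question asked twice, each time with half of the sessions.

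The label can also mislead. On day 7, a baseline labelled 0 mg comes from a participant who was offered 20 mg on day 5, and the reverse holds for the 20 mg label. A difference between the two by-dose results could be read as a dose effect, although any real difference could only come from chance, session day or the preceding session.

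At stake is the precision of the trial's view of disulfiram's own effect on mood and cardiovascular state. The protocol expects no enhanced cardiovascular response to cocaine under disulfiram, and that response is easier to interpret when the drug's effect before cocaine is well estimated.

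**Working it through.** **Inputs from the protocol.** The evaluable sample is 60 (Research Participants: "We anticipate that 75 volunteers will enter the study and that there will be a dropout rate of 20-30%, yielding a sample size of 60"). The detectable effect is "a difference of approximately 1/3 standard deviation units (d=.33) in differences in means across conditions", "using repeated measures analyses with power=.80 and two-tailed alpha=.05". The assumed correlation across conditions is rb = .5. There are two sessions per condition, on days 5 and 7.

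**Input not in the protocol.** The correlation rw between the two sessions of one visit is not given. I assume a range of .5 to .9.

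**The plan's own figure.** With rb = .5, the SD of a paired difference is √[2(1 − .5)] = 1 SD. The noncentrality is .33 × √60 = 2.556. A two-tailed paired t test (noncentral t, 59 df) then has power .71, not the stated .80. Taking f = .17 as d = .34 gives .74. One-tailed, d = .33 gives .81. The stated .80 is thus not reproduced two-tailed for a single paired contrast. That is a separate matter; here it only sets the starting value of .71.

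**By-dose contrast on the baseline (one session per condition).** The variance is 2(1 − rb) = 1.0 SD², so power is .71 for each dose. It would be .60 if Bonferroni were applied over the two doses.

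**Condition main effect (mean of both sessions per condition).** The variance is 2[(1 + rw)/2 − rb] SD². With rb = .5 this equals rw, and the noncentrality is 2.556/√variance.

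| rw (assumed) | Variance, SD² | Noncentrality | Power |
|---|---|---|---|
| .5 | 2(.75 − .5) = .5 | 3.61 | .94 |
| .6 | 2(.80 − .5) = .6 | 3.30 | .90 |
| .7 | 2(.85 − .5) = .7 | 3.06 | .85 |
| .8 | 2(.90 − .5) = .8 | 2.86 | .80 |
| .9 | 2(.95 − .5) = .9 | 2.69 | .76 |

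A simulation of 20,000 trials with all correlations at .5 gave .71 for each by-dose contrast and .944 for the averaged one. The difference detectable with 80% power is .368 SD by dose. Averaged, it is .260 SD at rw = .5 and .349 SD at rw = .9.

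**Day-1, day-4 and day-8 recordings.** Each day gives one value per condition, and none of them belongs to a dose. Day 1 precedes that visit's study drug. Day 4 is on drug and before that visit's cocaine. Day 8 follows both choice sessions and the stopping of study drug on day 7. If these recordings are outcomes, the same-visit day-1 value can serve as a covariate. The correlation between the baseline difference and the response difference is 2(rw − .5)/[2(1 − .5)], with rw now the correlation between two days of one visit. For rw = .6, .7 and .8 this is .2, .4 and .6, so variance falls by .04, .16 and .36.

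**The case against.** The strongest reply is that the model in the Statistical Analysis section already contains the better test. In a complete two-by-two within-subject ANOVA, the condition main effect is the paired test on each participant's two-session mean. The model loses nothing, and the by-dose comparisons could be read as additions to it. This stands, and it limits the point: the protocol offers two different tests of the same measure, and the one it calls planned is the weaker.

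A reader might infer that the information is simply halved. That is exact only if same-visit sessions correlate no more strongly than sessions in different visits. At rw = .8 or .9 the gain in power is modest.

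A reader might also infer that the day-1, day-4 and day-8 recordings are forced into a model that cannot be fitted, or are diluted by pooling day 1 with the later days. The protocol does not support either. The recordings are not listed as dependent measures, no text pools the days, and only a broad reading of the phrase on separate analyses for each outcome would bring them under the dosage factor. Their analysis may be set out in an analysis plan that is not shown.

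Finally, the two session baselines are not fully interchangeable, because day 7 follows the day-5 session. This also stands, and is why session day belongs in the model.

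**Conclusion.** The point holds for the pre-session baseline. As written, its planned comparisons are two by-dose contrasts with power .71 each, although a single contrast averaging both sessions is available from the same data and model, with power from .94 (rw = .5) down to .76 (rw = .9). These figures assume 60 complete participants, a true difference of .33 SD that is equal in both sessions, rb = .5 and two-tailed alpha .05. The averaged contrast is more precise at every value of rw shown; how much more depends on a correlation that the protocol does not give.

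For the day-1, day-4 and day-8 recordings no error is shown. A recommendation applies only if they are analysed as outcomes. Nothing here touches the analysis of cocaine choice.

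**What to change.** 1. In the Experiments section, limit the comparisons at each dose to measures taken after cocaine is offered.
2. For the baseline measure, name the condition main effect (disulfiram versus placebo on the two-session mean) as the planned comparison, with session day (5 or 7) in the model.
3. State whether the day-1, day-4 and day-8 recordings are outcomes. If they are, analyse them by condition and study day without a dosage factor, with contrasts at day 4 and at day 8 and the same-visit day-1 value as covariate. For participants who stay in hospital between parts, say which recording serves as the day-1 value of part 2, since the schedule lists none on day 9.

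The cost is a few sentences and one or two further model specifications, with no new data. The small downside is that the outcomes no longer share one set of contrasts.
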